### Inclusion criteria

HIV-infected participants must be ≥40 years of age or have HIV infection lasting for at least 15 years (proven by anti-HIV antibody test) at the time of enrollment, be able to provide informed consent and have a life expectancy of at least 1 year. Control group participants must be ≥40 years of age, be able to provide informed consent and have a life expectancy of at least 1 year.

### Interventions and comparisons

This is an observational study, so no study intervention is planned. Participants will receive usual care from their treating physicians throughout the study period.

### Study visits

Patients will be followed yearly for 3 years (baseline, year 1 and year 2), then have additional visits at years 5 and, depending on their recruitment date, at year 8. At each study visit, participants will complete study questionnaires, have a complete medical history and physical examination by a physician, have a panel of blood tests and an electrocardiogram. Twice during the study (year 1 and final year), participants will also undergo a dual energy X-ray absorptiometry to measure bone mineral density. In addition, all participants will be invited to contribute to a research blood bank, to which they will contribute serum and cells. Depending on availability at research sites, participants will also be invited to undergo leukapheresis, to maximize the number of white blood cells available in the biobank. Throughout follow-up, participants’ eligibility to the pre-planned sub-studies will be assessed, and patients will be offered participation in the sub-studies (presented below). Additional files 2 and 3 present tasks performed at each study visit and list of blood tests obtained, respectively.

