### Secondary outcomes

Secondary outcomes are: i)incidence of all-cause mortality, ii)incidence of major adverse cardiac and cerebrovascular events (MACE - composite outcome composed of cardiovascular death, MI, coronary revascularization or stroke), iii)incidence of individual components of the primary outcome, iv)incidence of the metS, v)incidence of type 2 diabetes, vi)incidence of renal failure, vii)incidence of abnormal bone mineral density and body fat distribution.

Complete definitions of outcomes are available in Additional file 1.

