### Primary outcome

Longitudinal analyses of the CVD incidence/prospective analysis: This analysis will use prospective data and will focus on time until occurrence of the first incident CVD event, as defined by the composite outcome described above. It will be limited to subjects without a history of CVD at cohort entry. Analyses will employ time-to-event statistical methods including Cox proportional hazards (PH) model [33] and its flexible extensions. Time 0 will be defined as the cohort entry and subjects who do not develop CVD during the follow-up will be right-censored at the earliest of times of: loss to follow-up, administrative end of the study or a non-CVD death**.** In all models, the binary indicator of HIV infection will be the main ‘exposure’ and its effect on the risk (hazard) of incident CVD will be adjusted for “standard confounders”: age, sex, ethnicity, education, income, and illicit drug use. However, two different types of models will handle differently the CVD risk factors, to provide a better understanding of the mechanisms through which HIV infection may affect future CVD risks. The first model will adjust the effect of HIV for only the baseline values of CVD risk factors, in addition to “standard confounders”. This will allow us to estimate and test the potential differences in CVD incidence between HIV+ vs. HIV- individuals who had the same initial values of common CVD risk factors, at cohort entry. In contrast, the second model will adjust for the up-dated values of CVD risk factors, modeled by time-varying covariates, representing the most recent value observed until a given date during the follow-up. This model will permit testing if there is a ‘residual’ impact of HIV infection that is *not* mediated through longitudinal changes in common CVD risk factors. The independent association between HIV and CVD incidence will be then estimated through the adjusted HR, with 95% confidence intervals (CI). In both analyses the proportional hazards assumption we will be tested using a flexible extension of the Cox model [34, 35].

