### Secondary outcomes

Incidence rates of secondary outcomes will be modeled as described for the primary outcome, through adjusted multivariable survival models.

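### Bone density has no scan at cohort entry, yet its incidence is to be modelled from entry, so undiagnosed abnormality already present would count as an incident event at year 1

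*Protocol article*

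**What the plan says.** Four statements in the protocol article bear on this outcome.

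- **Outcome** (Secondary outcomes): the last item listed is "incidence of abnormal bone mineral density and body fat distribution".
- **Measurement** (Study visits): "Twice during the study (year 1 and final year), participants will also undergo a dual energy X-ray absorptiometry to measure bone mineral density". The visit schedule itself is "Patients will be followed yearly for 3 years (baseline, year 1 and year 2), then have additional visits at years 5", with a year-8 visit for some participants according to when they were recruited. The final year is therefore 5 or 8.
- **Model** (Statistical analysis, Secondary outcomes): "Incidence rates of secondary outcomes will be modeled as described for the primary outcome, through adjusted multivariable survival models". No exception is made for bone density.
- **What that model is** (Statistical analysis, Primary outcome): "Time 0 will be defined as the cohort entry", and of the analysis set, "It will be limited to subjects without a history of CVD at cohort entry". Participants without an event are right-censored.

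Full outcome definitions are referred to Additional file 1, which is not shown. Under Covariates and data collection, the baseline visit records past and current medical conditions and medication. No scan is mentioned there.

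**The concern.** An incidence analysis needs each participant's outcome status at time 0. For CVD the article obtains it from history and removes prevalent cases. Bone density is established by a scan, and the first scan comes a year after the clock starts. A participant who entered with abnormal but undiagnosed bone density looks outcome-free at entry, stays in the risk set, and is recorded as an event at year 1.

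The hazard ratio for HIV would then mix two quantities: the difference in bone disease acquired before enrolment, and the difference in new disease during follow-up. If HIV-positive participants enter with more undiagnosed abnormality, the ratio can exceed 1 with no difference in new onset. If entry prevalence is equal, a real difference in new onset is diluted.

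Timing is also poorly known after year 1. With one further scan, onset is known only to fall in a window of 5 - 1 = 4 or 8 - 1 = 7 years.

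**Working it through.** The article states no rate, sample size or power for bone density, so there is no figure of its own to reproduce. The conflict follows from the text. Its size needs assumptions.

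**Can the plan be carried out as written?**

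1. The carried-over model needs participants free of abnormal bone density at cohort entry.
2. The only information at entry is medical history and medication, which identifies diagnosed disease only.
3. The first objective measurement is at year 1, so undiagnosed abnormality at entry cannot be separated from onset during the first year.
4. With time 0 at entry, both are events found at year 1.

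**How large is the prevalent share?**

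Assumptions, none from the article: fraction abnormal at the year-1 scan q = 15% to 25%; constant true hazard i = 1% to 2% per year; last scan at T = 5 or 8 years; everyone scanned; no one excluded for diagnosed disease.

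- Abnormal at entry: p = 1 - (1 - q)·exp(i). This removes first-year onsets from q.
- Abnormal at either scan: D = 1 - (1 - q)·exp(-i(T - 1)).
- Prevalent share of all detected events: p / D.

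| q | i | p | D, T = 5 | Share, T = 5 | D, T = 8 | Share, T = 8 |
|---|---|---|---|---|---|---|
| 15% | 2% | 1 - 0.85·1.0202 = 0.133 | 1 - 0.85·0.9231 = 0.215 | 62% | 1 - 0.85·0.8694 = 0.261 | 51% |
| 25% | 1% | 1 - 0.75·1.0101 = 0.242 | 1 - 0.75·0.9608 = 0.279 | 87% | 1 - 0.75·0.9324 = 0.301 | 81% |

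These two rows are the extremes. Among abnormalities found at the year-1 scan alone, the share already present at entry is 0.133/0.15 = 89% in the first row and 0.242/0.25 = 97% in the second.

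A wider set of assumptions (entry prevalence 10-50%, incidence 1-4% per year) gives 38-95% of all detected events with a last scan at year 5 and 29-93% at year 8. Even then, 74-99% of the year-1 abnormalities were present at entry.

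**What does it do to the comparison?**

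Suppose true incidence is equal in the two groups (HR = 1) and undiagnosed prevalence at entry is 20% in controls and 30% in HIV-positive participants (assumed). Counted from entry, the 5-year cumulative hazard in a group is H = -ln(1 - p) + 5i.

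- i = 1%: (0.357 + 0.05) / (0.223 + 0.05) = 0.407/0.273 = 1.49.
- i = 4%: (0.357 + 0.20) / (0.223 + 0.20) = 0.557/0.423 = 1.32.

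A true null would appear as a ratio of about 1.3 to 1.5. A fitted Cox ratio would not equal this figure exactly, because the whole excess arises at the year-1 scan and none after it.

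**The case against.** The strongest reply is that the article condenses a longer protocol. Additional file 1 holds the outcome definitions and may define incident abnormality relative to the year-1 scan. That is possible, but such a definition would contradict the stated time origin, and the analysis text would still need an exception. No definition can supply a scan at entry.

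Other parts of the defence stand and limit the point:

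- A reader might infer that every abnormal year-1 scan becomes an event. The text does not support this. The restriction to outcome-free participants carries over with the model, and baseline history allows diagnosed bone disease to be excluded. The problem is undiagnosed abnormality.
- A reader might infer that the plan commits to a Cox model with the scan date as event date. It does not. The article speaks of time-to-event methods that include Cox and its extensions, and for secondary outcomes only of survival models. An interval-censored model is not ruled out. The fault lies in the time origin and risk set.
- A reader might say that body fat distribution has no incidence. In the outcome list, the word abnormal can govern both nouns, and anthropometry is taken at baseline and repeated. No such claim is made here.
- A reader might treat every year-1 abnormality as prevalent and consider only a year-5 last scan, giving roughly 70-89%. That ignores first-year onset and the year-8 scan. The corrected ranges are lower.
- The study hypothesis names CVD, metabolism and immune senescence, not bone. Early osteoporosis appears only in the Background as a comorbidity of concern.

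**Conclusion.** The point holds for one secondary outcome. The scan schedule, the incidence definition, the time origin at entry and the outcome-free risk set cannot all be applied to bone density. As written, undiagnosed abnormality at entry is counted as incident at year 1.

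The size rests on assumed rates. Under the assumptions of 15-25% abnormal at year 1 and 1-2% per year, at least about half of detected events would be prevalent. Under the wider assumptions the share can fall below half, so it would be too strong to say that the hazard ratio must be mainly a prevalence comparison. The spurious ratio of 1.3 to 1.5 likewise needs a difference in undiagnosed prevalence, which the article neither states nor excludes. Excluding diagnosed cases would reduce both effects by an unknown amount.

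The primary CVD analysis and its power are untouched.

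**What to change.** In Statistical analysis, Secondary outcomes, add an exception for bone density:

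1. Take the year-1 scan as the bone baseline and as time 0 for this outcome.
2. Report abnormality at year 1 by HIV status as prevalence.
3. Estimate incidence only among participants normal at year 1, with an interval-censored survival model. One example is complementary log-log regression on status at the second scan with log time between scans as offset, which handles 4- and 7-year gaps together if the hazard is constant within the interval.
4. Analyse change in bone density between scans, adjusted for the year-1 value.
5. Align the definition in Additional file 1 with this wording.

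The cost is analysis wording and some precision; no new scan is required. Under the assumed rates, new cases between year 1 and year 5 would be 0.75·(1 - exp(-0.04)) = 2.9% to 0.85·(1 - exp(-0.08)) = 6.5% of those scanned. That is 29 to 65 per group of 1000 before any loss. The incidence estimate also depends on who survives and returns for the second scan, and the report should acknowledge this.

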### Covariates and data collection

At the baseline visit, data will be collected (and entered into the electronical case report form) on socio-demographic factors, all past and current medication, all past and current medical conditions (including high blood pressure, diabetes, dyslipidemia, family history of premature CVD), presence of risk factors for HIV transmission, and lifestyle habits (smoking, alcohol consumption, illicit drug use and level of physical activity). For participants with HIV, date of diagnosis and presumed mode of transmission will also be recorded. A complete physical examination will be performed by the treating physician, and the study nurse will record vital signs, height, weight, and waist circumference.

At the subsequent yearly visits, data on medical history, medication history and lifestyle habits will be updated. Anthropometric measures and physical examination will be repeated. Data on primary and secondary outcomes will be recorded using specific case report forms. Additional file 4 presents the full contents of the case report form that will be filled out at each study visit.

### Statistical considerations

#### Power calculation

Based on data from both our local HIV database and our pilot study [27, 28], we expect the HIV positive population to be 80% male, with a mean age of 50 years at the beginning of the study. Based on data from the Framingham study, expected rates of our primary outcome in HIV-negative participants are 10/1000 person-years for men and 4/1000 person-years for women in the 45–54 age group [29]. The rates more than double for the 55–64 age group [29]. Accordingly, we assume the overall CVD incidence rate in HIV-negative controls will range between 8/1000 PY and 12/1000 PY. Analysis for the primary outcome will be limited to subjects who are free of CVD at baseline. We expect that, at baseline, up 10% of HIV- and 15% of HIV+ subjects will have prevalent CVD [29]. Finally, we assume that an average CVD-free subject will contribute 4 years of follow-up (of the maximum potential follow-up of 5 years). Under these assumptions, the recruitment of 1000 subjects in each group (implying that 900 HIV- and 850 HIV+ subjects will be free of CVD at baseline, contributing 3600 and 3400 PY of follow-up) will yield 80% power with alpha = 0.05 to detect hazard ratios of 1.72 to 1.90 for the primary composite outcomeof CVD. These risk increases are clinically plausible and are actually lower than the more than 2-fold (HR > 2.0) increases in the risk of major CVD events associated with HIV infection [30]. Some studies have reported higher HRs for specific sub-populations or CVD events, e.g. HR 4.0 for risk of stroke among younger subjects [31]. All sample size calculations were done with the PASS software [32].

### Statistical analysis

The analyses will focus on comparing the incidence of CVD in HIV+ subjects and comparing it to the incidence of CVD in HIV- controls.

### Primary outcome

Longitudinal analyses of the CVD incidence/prospective analysis: This analysis will use prospective data and will focus on time until occurrence of the first incident CVD event, as defined by the composite outcome described above. It will be limited to subjects without a history of CVD at cohort entry. Analyses will employ time-to-event statistical methods including Cox proportional hazards (PH) model [33] and its flexible extensions. Time 0 will be defined as the cohort entry and subjects who do not develop CVD during the follow-up will be right-censored at the earliest of times of: loss to follow-up, administrative end of the study or a non-CVD death**.** In all models, the binary indicator of HIV infection will be the main ‘exposure’ and its effect on the risk (hazard) of incident CVD will be adjusted for “standard confounders”: age, sex, ethnicity, education, income, and illicit drug use. However, two different types of models will handle differently the CVD risk factors, to provide a better understanding of the mechanisms through which HIV infection may affect future CVD risks. The first model will adjust the effect of HIV for only the baseline values of CVD risk factors, in addition to “standard confounders”. This will allow us to estimate and test the potential differences in CVD incidence between HIV+ vs. HIV- individuals who had the same initial values of common CVD risk factors, at cohort entry. In contrast, the second model will adjust for the up-dated values of CVD risk factors, modeled by time-varying covariates, representing the most recent value observed until a given date during the follow-up. This model will permit testing if there is a ‘residual’ impact of HIV infection that is *not* mediated through longitudinal changes in common CVD risk factors. The independent association between HIV and CVD incidence will be then estimated through the adjusted HR, with 95% confidence intervals (CI). In both analyses the proportional hazards assumption we will be tested using a flexible extension of the Cox model [34, 35].

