### Study hypothesis

The chronic and persistent inflammation associated with HIV disease leads to accelerated aging, characterized by premature CVD, altered metabolism and immune senescence. This will translate into higher incidence rates of CVD in HIV infected participants, when compared to HIV negative participants, after adjustment for traditional CVD risk factors. When characterized further using cardiovascular imaging, biomarkers, immunological and genetic profiles, CVD associated to HIV will show different characteristics compared to CVD in HIV-uninfected individuals.

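### The second Cox model uses latest in place of baseline CVD risk-factor values, which does not match its reading as the HIV effect not carried by risk-factor change

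*Protocol article*

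**What the plan says.** Under Statistical analysis, Primary outcome, the Protocol article specifies two Cox models. All models carry age, sex, ethnicity, education, income and illicit drug use. They differ in how they treat CVD risk factors:

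- First model: "The first model will adjust the effect of HIV for only the baseline values of CVD risk factors", on top of those confounders. It compares people who started from the same risk-factor values.
- Second model, introduced as a contrast to the first: "the second model will adjust for the up-dated values of CVD risk factors, modeled by time-varying covariates, representing the most recent value observed" up to each point in follow-up.

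The second model is meant to test for a remaining HIV effect that is not "mediated through longitudinal changes in common CVD risk factors".

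The Study hypothesis section predicts higher CVD incidence in HIV-infected participants "after adjustment for traditional CVD risk factors". The Secondary outcomes section under Statistical analysis says those outcomes will be modelled in the same way.

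**The concern.** The two models are set against each other, and nothing says that a baseline risk-factor term stays in the second. Blood pressure, lipids, diabetes and smoking are not among the covariates kept in every model. On the natural reading, the latest value takes the place of the baseline value, so the models are not nested.

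The stated inference concerns change. The latest value equals the starting value plus the change since then. Separating out the part of the HIV effect that runs through change requires the starting value to be held fixed. The first model does this and the second does not.

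Two things are at stake. A shift in the HIV HR between the models cannot be read as mediation by risk-factor change. And if earlier exposure has lasting effects beyond the current reading (for example, years of high pressure or lipids since treated), part of an entry difference between the groups can fall on the HIV term.

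**Working it through.** **1. The plan's own figures.** The inputs come from the Power calculation section: 3600 and 3400 person-years, 900 and 850 CVD-free subjects, and control rates of 8 to 12 per 1000.

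- Events at HR 1.90: 3600 × 0.008 + 3400 × 0.008 × 1.90 = 80.5. Schoenfeld power (two-sided 0.05, share exposed 850/1750) is 82.1%; Freedman gives 79.5%.
- Events at HR 1.72: 3600 × 0.012 + 3400 × 0.012 × 1.72 = 113.4. Power is 82.3% and 80.5% respectively.

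The stated 80% is reproduced and does not depend on this point. The standard error of the log HR, 1/√(events × 0.486 × 0.514), is about 0.22 at 80.5 events and 0.19 at 113.4.

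**2. When the second model is biased.** Suppose HIV has no direct effect and the log hazard is b0·X0 + bt·Xt for a standardised factor with baseline value X0 and latest value Xt. Let their within-group correlation be ρ, the group gap at entry d, and the later gap dt. Given Xt and HIV status, the expected X0 is ρ·Xt plus, for HIV+, d − ρ·dt. With X0 left out, the HIV coefficient is therefore about

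b0 × (d − ρ·dt).

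- Only the latest value matters (b0 = 0): no bias.
- Gap persists (dt = d): b0·d·(1 − ρ), upward for a positive gap.
- Gap shrinks with tracking (dt = ρ·d): b0·d·(1 − ρ²), larger.
- Groups equal at entry, then drifting apart (d = 0): −b0·ρ·dt, downward when HIV+ drift to higher levels.

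**3. Size, four factors.** Assumptions not in the documents: b0 = 0.3 per SD, d = 0.2 to 0.3 SD, ρ = 0.5 to 0.7, four independent factors shifted the same way. At years 0 to 1 the latest value is the baseline value, so with 4 years of average follow-up about three quarters of the time is exposed to the bias.

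| d, ρ | Gap | 4 × coefficient | HR, whole follow-up | × 3/4 | HR |
|---|---|---|---|---|---|
| 0.2, 0.7 | persists | 0.072 | 1.07 | 0.054 | 1.06 |
| 0.3, 0.6 | persists | 0.144 | 1.15 | 0.108 | 1.11 |
| 0.3, 0.5 | persists | 0.180 | 1.20 | 0.135 | 1.14 |
| 0.2, 0.7 | shrinks | 0.122 | 1.13 | 0.092 | 1.10 |
| 0.3, 0.6 | shrinks | 0.230 | 1.26 | 0.173 | 1.19 |
| 0.3, 0.5 | shrinks | 0.270 | 1.31 | 0.203 | 1.22 |

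Simulation of the four-factor case, also with bt = 0.3 and latest equal to baseline in year 1, gave about 1.03 to 1.13 when the gap persists and 1.09 to 1.20 when it shrinks. These ends lie within 0.03 of the last column. With baseline and latest values both in the model the HR was about 1.0.

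**4. Size, one factor.** Updates at years 1 and 2, last value carried to year 5, total log HR 0.5 per SD, true HIV HR 1.00:

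| Scenario | HR, latest only | HR, baseline + latest |
|---|---|---|
| Only the latest value matters, 0.5 SD gap | 1.00 | 1.00 |
| Baseline and latest matter equally, 0.5 SD gap, tracking 0.8 | 1.03–1.06 | 1.00 |
| Same, tracking 0.5 | 1.07–1.10 | 1.00 |
| Baseline dominates, 0.5 SD gap, tracking 0.8 | 1.05–1.09 | 1.00 |
| Same, tracking 0.5 | 1.11–1.17 | 1.00 |
| Equal effects, 0.2 SD gap, tracking 0.8 | 1.01 | 1.00 |
| Equal at entry, then drift, tracking 0.8 | 0.95 | 1.00 |

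**The case against.** - **The article is condensed.** It does not say in so many words that baseline terms are dropped, and a full analysis plan may list the covariates. That would excuse missing detail. But the article itself fixes both the form of the covariates and the inference drawn from them, and the two do not match.
- **Entry differences are not left uncontrolled.** A reader might infer that they necessarily leak into the residual HIV HR. The documents do not support that. The latest value is the baseline value until the first update and carries much of it afterwards. Leakage needs a separate effect of past level, on which the documents give no figure. This part of the objection stands.
- **The size is modest.** The whole-follow-up column reaches 1.31, but it ignores the first year and takes the shrinking-gap case. With a persisting gap, the year-1-weighted log bias of 0.05 to 0.14 is below one standard error of 0.19 to 0.22. The scenario also needs four factors all shifted the same way, and smoking is frequency matched. This stands, although blood pressure, lipids and diabetes are not matched.
- **Latest-value adjustment is a standard time-varying Cox model.** True. It validly estimates the HIV effect at equal current levels, which is a different quantity from the one the article names.

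**Conclusion.** The point holds as a mismatch between model and interpretation. As written, the second model does not isolate risk-factor change, and the step from the first model to the second cannot be read as mediation by such change. That conclusion rests on the text alone.

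The bias is conditional on past levels mattering and on the groups differing at entry or drifting apart. Under the assumptions in the working, the false residual HR is about 1.03 to 1.20. It can fall below 1 (0.95 in one drift scenario), and it is 1.00 if only the latest value matters.

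It would go too far to say that the study's main hypothesis is undermined. The first model, which adjusts for baseline risk factors, addresses that hypothesis directly and is unaffected. The second is its mechanistic companion.

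**What to change.** Define the second model as the first model plus the updated values: keep each baseline risk-factor value and add its most recent value, or its change since baseline, as a time-varying term. Base the residual HIV HR on that model, for the primary outcome and for the secondary outcomes modelled in the same way.

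If the latest-value-only model is kept, describe its HR as the HIV effect at equal current risk-factor levels, and do not interpret the shift from the first model as mediation by risk-factor change.

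The cost is a sentence of analysis wording and no new data, since baseline values are already collected. The model gains about one parameter per risk factor, with roughly 80 to 113 events expected. The HIV interval should widen negligibly: in simulation at about 65 to 80 events, the standard error of the HIV log HR was about 0.25 with or without the baseline terms.

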**Methods/design:**

The Canadian HIV and Aging cohort is a prospective, controlled cohort study funded by the Canadian Institutes of Health Research. It will recruit patients living with HIV who are aged 40 years or older or have lived with HIV for 15 years or more. A control population, frequency matched for age, sex, and smoking status, will be recruited from the general population. Patients will attend study visits at baseline, year 1, 2, 5 and 8. At each study visit, data on complete medical and pharmaceutical history will be captured, along with anthropometric measures, a complete physical examination, routine blood tests and electrocardiogram. Consenting participants will also contribute blood samples to a research biobank. The primary outcome is incidence of a composite of: myocardial infarction, coronary revascularization, stroke, hospitalization for angina or congestive heart failure, revascularization or amputation for peripheral artery disease, or cardiovascular death. Preplanned secondary outcomes are all-cause mortality, incidence of the metabolic syndrome, incidence of type 2 diabetes, incidence of renal failure, incidence of abnormal bone mineral density and body fat distribution. Patients participating to the cohort will be eligible to be enrolled in four pre-planned sub-studies of cardiovascular imaging, glucose metabolism, immunological and genetic risk profile.

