### Analyses restricted to HIV+ cohort

#### Effect of antiretroviral therapy

To estimate the effect of antiretroviral medication on CVD risk, supplementary analysis will be performed in the cohort of HIV-infected individuals. Incidence rates of the primary outcome will be modeled using survival models similar to those described for the primary outcome, but with drug exposure as the main exposure variable. Drug exposure will be captured as time-dependent variables capturing cumulative exposure, updated for each month of exposure. Models of CVD risk according to exposure to individual drugs will be fitted for abacavir, tenofovir, efavirenz, atazanavir, lopinavir, darunavir, raltegravir, dolutegravir and elvitegravir. These drugs will be analyzed individually due to past signals of cardiovascular toxicity, prevalence of use in our cohort or insufficient data on cardiovascular toxicity available in the literature [21, 36–41]. Exposure to other antiretrovirals will be examined by drug class, as opposed to individually, because we would have insufficient power to detect effect of individual drugs.

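### Model 2 carries risk factors forward across a three-year visit gap, so HIV-differential change after year 2 stays in the coefficient the protocol reads as not mediated; the bias can run either way

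*Protocol article*

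**What the plan says.** All references are to the protocol article.

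- **Covariate rule.** Under Statistical analysis, Primary outcome, the first model adjusts for baseline CVD risk factors. The second adjusts for updated values, "modeled by time-varying covariates, representing the most recent value observed until a given date during the follow-up".
- **Purpose.** The same paragraph says of the second model: "This model will permit testing if there is a ‘residual’ impact of HIV infection that is" not mediated through longitudinal change in the common risk factors.
- **Schedule.** The Abstract (Methods/design) states: "Patients will attend study visits at baseline, year 1, 2, 5 and 8". Study visits agrees: "Patients will be followed yearly for 3 years (baseline, year 1 and year 2), then have additional visits at years 5", with year 8 depending on recruitment date.
- **Data updates.** Covariates and data collection states: "At the subsequent yearly visits, data on medical history, medication history and lifestyle habits will be updated". Measurements and examination are repeated at these visits. The word *yearly* fits the schedule only up to year 2, and no contact between years 2 and 5 is described.
- **Follow-up.** Power calculation assumes an average of 4 years "of the maximum potential follow-up of 5 years".
- **Dated data elsewhere.** Antiretroviral exposure is to be "updated for each month of exposure" (Effect of antiretroviral therapy), and the Sensitivity analysis obtains dates of past CVD retrospectively from the baseline history.

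**The concern.** The updating rule, the schedule and the interpretation are all stated, so this is not a detail left to an unseen analysis plan. Together they do not support the inference drawn. After year 2 the model sees no new risk-factor value until year 5. If risk factors change in that gap at different rates in the two groups, the resulting difference in CVD hazard cannot be credited to the risk factors and stays with HIV.

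The mediation claim is what is at stake. The study hypothesis is that HIV raises CVD risk beyond traditional risk factors, and model 2 is the protocol's test of that. A residual HR moved by the visit gap could be taken for a non-traditional pathway, or could hide one. The Discussion of methodological limits does not mention the gap.

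**Working it through.** **1. The plan's own figure.** CVD-free subjects: 900 × 4 = 3600 PY (HIV-) and 850 × 4 = 3400 PY (HIV+). Wald test on the log rate ratio, two-sided 0.05:

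- 12/1000 PY, HR 1.72: events 43.2 and 3400 × 0.012 × 1.72 = 70.2; SE = √(1/43.2 + 1/70.2) = 0.193; ln 1.72 / SE = 2.80; power 0.80.
- 8/1000 PY, HR 1.90: events 28.8 and 51.7; SE = 0.233; ln 1.90 / SE = 2.76; power 0.79.

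The stated range of 1.72 to 1.90 reproduces. It does not depend on how model 2 updates covariates; it is used here only for the 4- and 5-year follow-up.

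**2. Time covered by the year-2 value.** Followed 4 years: (4 − 2)/4 = 50%. Followed 5 years: (5 − 2)/5 = 60%. The share of time using a value more than one year old is 1/4 = 25% and 2/5 = 40%.

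**3. Share of mediated effect unseen.** Assume that the HIV-related difference in risk factors grows linearly from entry, adding g per year to the log hazard, and that events are rare enough to average evenly over follow-up. Model 1 leaves g × (mean time since entry) in the HIV coefficient. Model 2 leaves g × (mean age of the carried-forward value), where mean age = Σ(gap²/2)/T. The unseen share is the ratio of the two, and g cancels.

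| Follow-up T | Planned visits: mean lag | Mean time | Unseen | Unseen with yearly visits |
|---|---|---|---|---|
| 4 y | (0.5+0.5+2)/4 = 0.75 | 2.0 | 37.5% | 0.5/2.0 = 25% |
| 5 y | (0.5+0.5+4.5)/5 = 1.1 | 2.5 | 44% | 0.5/2.5 = 20% |
| 8 y | (0.5+0.5+4.5+4.5)/8 = 1.25 | 4.0 | 31% | 0.5/4.0 = 12.5% |

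With censoring uniform over 3 to 5 years the shares are 39% against 23%; with exponential loss giving a 4-year mean, 43% against 21%.

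**4. Simulated check.** Cox model, 150,000 subjects, baseline hazard 10/1000 PY, censoring uniform over 3 to 5 years, true direct HR of 1, SE of log HR about 0.025. The drift of 0.10 per year on the log hazard is an assumption.

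| Faster drift in | Baseline only | Planned visits | Yearly visits | True current value |
|---|---|---|---|---|
| HIV+ | 1.279 | 1.117 | 1.077 | 1.024 |
| HIV- | 0.807 | 0.920 | 0.955 | 1.002 |
| neither | 0.967 | 0.967 | 0.967 | 0.967 |

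For drift in HIV+, the unseen share is (ln 1.117 − ln 1.024)/(ln 1.279 − ln 1.024) = 0.087/0.222 = 39%; with yearly visits it is 0.050/0.222 = 23%. Both match step 3. In the last row all four models give the same HR, about 1.4 SE from 1, so change common to both groups adds no bias.

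**5. Would truncating at year 3 help?** Lag = (0.5+0.5+0.5)/3 = 0.5; mean time 1.5; unseen 33%. That is close to the 37.5% at 4 years, so agreement between a truncated and a full analysis would say little.

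**The case against.** Carrying the last value forward is ordinary practice for time-varying Cox covariates, and any visit-based schedule leaves some change unseen. More than half of the leak would exist with yearly visits: 25 of 37.5 points at 4 years, 23 of 39 with censoring over 3 to 5 years. At 5 years it is 20 of 44, slightly under half. The effect is also small beside the sampling error. At 10/1000 PY, with 36 control events and about 44 in HIV+ (assuming a model 1 HR near 1.28), the SE of the log HR is √(1/36 + 1/44) = 0.225. A spurious HR of 1.12 is then about 0.5 SE, and the chance of a false positive rises from 5% to about 8%, against about 6% with yearly visits. These points stand. They limit the size of the problem but do not make the stated reading correct.

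Some stronger readings are tempting, and the documents do not support them:

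- **That the residual HR will be falsely raised.** The protocol gives no rates of risk-factor change by HIV status. The direction is unknown, and without a difference between groups there is no bias.
- **That a diagnosis or drug start at, say, year 2.5 will certainly be missed.** The rule speaks of observed values and does not say whether dated items enter at their date or at the visit. The case report form is in an additional file that is not shown. Only measured factors such as blood pressure, lipids and weight are unavoidably out of date.
- **That the year-5 value is never used.** That holds within the 5-year window of the power calculation, but participants seen at year 8 do use it.
- **That 44% applies throughout.** It needs everyone to be followed for 5 years; the planned mean is 4.

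**Conclusion.** The point holds in this form. The schedule and the updating rule do not let model 2 separate HIV effects that act through risk-factor change after year 2 from those that do not, and the protocol claims that separation without qualification. Under linear drift, 37.5% to 44% of the mediated log-HR is unseen over 4 to 5 years, against 25% to 20% with yearly visits, and about 31% for participants followed 8 years. The percentages rest on linearity and on visit-date updating of all risk factors. The HRs in the working rest also on an assumed drift and full mediation, for which the documents give no figures.

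A reader might take this as undermining the main HIV comparison. It does not: model 1, which adjusts for baseline values, and the power calculation are untouched. What needs changing is how model 2 is built and read.

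**What to change.** - **Dated risk factors.** In model 2, update diagnosis of diabetes, hypertension or dyslipidemia, start or stop of related drugs, and change in smoking at their calendar dates. The protocol already relies on dated histories for antiretroviral exposure and for past CVD.
- **Equal ascertainment.** A participant with a fatal event at year 4 has no year-5 visit at which to give a history. For anyone with an event before the next visit, fatal events included, take the same dated history from the event form or medical record. Censor participants lost to follow-up at last contact. Otherwise covariate ascertainment depends on the outcome.
- **Measured values.** Keep carry-forward only for blood pressure, lipids and weight.
- **Conclusion.** Limit it to an HIV effect not mediated through risk-factor changes captured by the visit schedule and dated history. Do not make agreement with an analysis truncated at year 3 the criterion, since about 33% is still unseen there.
- **Wording.** Reconcile the reference to yearly visits in Covariates and data collection with the schedule in the Abstract and in Study visits.

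No extra visit is needed. The cost is reliance on recall and records, some additional data derivation, and a narrower mediation claim.
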